#### Secondary outcomes

Pain intensity: Pain intensity is assessed using NRS at 1 min and 5 min after the start of ablation, at the end of the surgery, and at 2 h, 6 h, 12 h, 24 h, and 48 h after surgery (at rest, during coughing, or during activity).

Evaluation of the degree of analgesic satisfaction: (A) before leaving the operating room to assess the patient's satisfaction with the analgesic effect; (B) before leaving the operating room, the surgeon and surgical nurses implement the satisfaction assessment. The satisfaction score uses the visual analog scale (VAS), with a Vernier ruler of 10 cm in length, marked with 10 scales, 0 point and 10 points at both ends, respectively. The patient, surgeon, and surgical nurses mark the corresponding position representing their comfort on the ruler, and the follower score it according to the position marked by the patient. A score of 0 represents extreme dissatisfaction and a score of 10 represents extreme satisfaction.

Duration of surgery: Time from the start to the end of ablation is calculated in minutes.

Postoperative hospital stay: Time from the end of surgery to discharge is calculated in days.

Average daily dose: The ratio of total dose to days of medication is calculated in milligrams.

Uninterrupted completion rate of surgery without complaints of pain: The rate is calculated as follows:

$$\mathrm{Number}\;\mathrm{of}\;\mathrm{patients}\;\mathrm{with}\;\mathrm{uninterrupted}\;\mathrm{completion}\;\mathrm{of}\;\mathrm{surgery}\;\mathrm{and}\;\mathrm{without}\;\mathrm{complaints}\;\mathrm{of}\;\mathrm{pain}/\mathrm{total}\;\mathrm{number}\;\mathrm{of}\;\mathrm{cases}\;\times\;100\%$$

Quality of life assessment: One week after surgery, quality of life is assessed through a telephone interview (using EORTC Quality of Life Inventory QLQ-C30 (V3.0), Additional file 1).

### Participant timeline {13}

Time schedule of enrolment, interventions, assessments, and visits for participants, see Additional file 2.

### Sample size {14}

The sample size and case allocation included patients who underwent tumor ablation. NRS score (at rest) ≤ 3 points during operation and within 48 h after the operation was defined as effective. Assuming that the effective rate was 90% in the nalbuphine group and 90% in the morphine group, the clinical cut-off value for non-inferiority between the two groups was 10% if the nalbuphine group is non-inferior to the morphine group, setting one-sided α-error level = 0.025, *β* = 0.2 (power = 0.8), and the sample size ratio of the two groups 1:1. Overall, 142 patients were required for each group calculated using the PASS15.0 software, and a total of 284 patients were required for the two groups. Based on the dropout rate of 10% (284 ÷ 0.9 = 316), a total of approximately 316 patients were planned to be included.

### Recruitment {15}

The study was performed based on open recruitment, and patients were screened according to the inclusion and exclusion criteria of the study.

## Assignment of interventions: allocation

### Sequence generation {16a}

The subjects are randomly assigned to the experimental group and the control group by computer-generated random numbers.

### Concealment mechanism {16b}

Only the patient’s random number and initials may appear on the electronic case report form. Random numbers are generated according to the interactive web response system.

### Implementation {16c}

Electronic Data Capture System will generate the allocation sequence, hospitals participating in the study will enroll participants, and research doctors in the hospital will assign participants to interventions.

## Assignment of interventions: blinding

### Who will be blinded {17a}

Among all trial participants and personnel, only patients who are enrolled will be blinded. They did not know what medications they were using.

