### Trial design {8}

This study is a superiority trial. We designed it by a multicenter, single-blind, randomized, parallel, positive-controlled clinical study to observe the efficacy and safety of nalbuphine hydrochloride injection and morphine hydrochloride injection for perioperative analgesia in tumor ablation. With such a study design, we hope to find a more effective and safe method of analgesia in the perioperative period for tumor ablation.

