### Criteria for discontinuing or modifying allocated interventions {11b}

During the study, the study can be terminated early/closed due to the following reasons: (1) Serious adverse events related to the test drug occurred during the study; (2) The effect of the drug was found to be too poor in the test, and there was no need to continue the study; (3) Major mistakes in the clinical trial protocol were found in the trial, and it was difficult to evaluate the drug effect; (4) The drug regulatory authority or the ethics committee requested to terminate the approved research.

An individual participant’s disenrollment criteria are as follows: (1) inability to complete the observation due to adverse events, (2) withdrawal invited by the investigator (poor compliance, serious adverse events), and (3) combination of prohibited drugs during the study period that prevented satisfaction and effectiveness evaluation.

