### Data management {19}

An electronic data capture system is used for data collection in this study. According to the GCP requirements for clinical trials in China, the data shall be maintained for 5 years after the termination of the clinical trial.The full analysis set (FAS) of the analysis dataset includes all subjects who were randomized, received the study drug, and had at least one efficacy evaluation data after medication. In case of missing data of the primary efficacy endpoint, the last observation carried forward is applied according to the intention-to-treat principle. The missing values for the comparability analysis and secondary efficacy measures are not carried forward and were based on the analysis dataset obtained in the FAS.Per protocol set (PPS) is a dataset generated from subjects who are fully compliant with the trial protocol; compliance includes receiving treatment, availability of the primary endpoint measures, and no major trial protocol violations. The per-protocol analysis is used mainly for the primary efficacy measures.Safety set (SS) refers to all subjects who are randomized, received the study drug, and have at least one post-baseline safety assessment.

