#### Statistical analysis method

The number of included and completed cases in the overall and each site is listed in the case analysis, and three analysis datasets (FAS, PPS, and SS) are generated. Dropouts and excluded cases along with the reasons for their dropping out and exclusion are listed.Demographic and baseline data analysis: Descriptive statistics of demographic data and other baseline characteristic values: For continuous variables, total number of cases, mean, standard deviation, median, and minimum and maximum values are calculated. The t-test will be used for normally-distributed data and the rank-sum test will be used for data with skewed distribution. Frequency and proportion are calculated for countable and grade data. The chi-square test will be used for disordered classification data, and the rank-sum test will be used for ordinal data. Inferential statistical results (*P*-values) are presented based on descriptive statistics.Efficacy analysis:A.Analysis of the primary efficacy indicators (overall response rate): The overall response rate is compared using the chi-square test, corrected chi-square test, or exact probability test. The 95% confidence interval of the difference in response rates between the two groups will be calculated, and if the lower limit of the confidence interval is greater than −10%, the result will be considered non-inferior.B.Analysis of the secondary efficacy indicators: Differences in the scores of NRS at each time point and the total score between the two groups are compared by the *t*-test or rank-sum test; differences in the physician satisfaction VAS score and the nurse satisfaction VAS score between the groups are compared by the t-test or rank-sum test; the difference between the two groups regarding willingness to undergo ablation surgery another time will be compared by the chi-square test, corrected chi-square test, or exact probability test; differences between the two groups with respect to duration of surgery, postoperative hospital stay, and average daily dose will be compared by the t-test or rank-sum test; the difference in the uninterrupted completion rate of surgery without complaints of pain between the groups will be compared by the chi-square test, corrected chi-square test, or exact probability test.Safety analysis: The incidence of adverse reactions will be calculated, their frequency and proportion were systematically listed, and the percentage calculated. A detailed list of cases of various adverse events (AEs), the number and rate of cases, conversion of physical examination indicators, ECG, respiratory and circulatory indicators, and laboratory indicators that “turn normal to abnormal” or “intensify abnormal” after the test, and list clinical explanations will be recorded.

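### The protocol blinds only patients, so nothing stops those who settle per-protocol membership from seeing arm and outcome; near the margin, one exclusion can flip the per-protocol non-inferiority result

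*Protocol article*

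**What the plan says.** Under Who will be blinded {17a}, the protocol article says "Among all trial participants and personnel, only patients who are enrolled will be blinded". Trial design {8} agrees, calling the trial a "multicenter, single-blind, randomized, parallel, positive-controlled clinical study".

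Data management {19} defines three sets.
- **Full analysis set (FAS):** randomized, dosed, and at least one efficacy value after dosing. Statistical methods {20a} uses the same rule for the outcome analysis.
- **Per-protocol set (PPS):** requires, among other things, "availability of the primary endpoint measures, and no major trial protocol violations". It is used mainly for the primary efficacy measure.
- **Safety set (SS):** randomized, dosed, and at least one safety assessment after baseline.

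Among the reasons for taking a participant out, {11b} lists "combination of prohibited drugs during the study period that prevented satisfaction and effectiveness evaluation", and also withdrawal at the investigator's invitation.

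Non-inferiority is declared if the lower limit of the 95% confidence interval for the difference in effective rates lies above -10% (Statistical analysis method). The article does not name the interval method.

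**The concern.** A condensed article may be silent on who masks the analysis. This one is not silent: it speaks of all personnel and restricts blinding to patients. An analysis plan that masked the statistician would therefore contradict {17a} as it stands.

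Whether a violation is major, and whether a prohibited drug prevented evaluation, are judgements about individual patients. As written, they can be made by people who know both the patient's arm and whether that patient was a treatment failure. In a non-inferiority trial, leaving out failures on the test drug favours the conclusion sought. If the result lies close to the margin, the trial could not show afterwards that knowledge of the arm played no part in settling the PPS.

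**Working it through.** **Inputs.** From Sample size {14}: "Assuming that the effective rate was 90% in the nalbuphine group and 90% in the morphine group"; a margin of 10 percentage points; "setting one-sided α-error level = 0.025"; power 0.80; allocation 1:1; 142 per group, or 316 in total after 10% dropout. From Statistical analysis method: the lower 95% limit must exceed -10%. I take the difference as nalbuphine minus morphine.

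**1. The plan's own figure.** n = (1.960 + 0.842)² × (0.9×0.1 + 0.9×0.1) / 0.10² = 7.85 × 0.18 / 0.01 = 141.3, rounded up to 142 per group. 284 / 0.9 = 315.6, rounded up to 316. Both agree with the article.

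**2. One exclusion at the margin.** Wald lower limit: L = p₁ − p₂ − 1.96 × √[p₁(1−p₁)/n₁ + p₂(1−p₂)/n₂].
- Before: p₁ = 124/142 = 0.8732 and p₂ = 128/142 = 0.9014. The difference is -0.0282 and the standard error 0.0375, so L = -0.0282 − 0.0735 = -0.1016. This fails.
- After excluding one nalbuphine failure: p₁ = 124/141 = 0.8794. The difference is -0.0220 and the standard error 0.0371, so L = -0.0220 − 0.0728 = -0.0947. This passes.

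**3. Does it depend on the interval method or the sample size?**

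| Per arm | Failures, nalbuphine v morphine | Method | Before | After one exclusion |
|---|---|---|---|---|
| 142 | 18 v 14 | Wald | -10.16% | -9.47% |
| 142 | 18 v 14 | Newcombe-Wilson | -10.37% | -9.69% |
| 158 | 21 v 16 | Wald | -10.25% | -9.64% |
| 158 | 21 v 16 | Newcombe-Wilson | -10.41% | -9.81% |

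One exclusion moves the limit by 0.6 to 0.7 points. It is not always enough: with 13 morphine failures and 142 per arm, the first failing nalbuphine count (18) does not flip under Wald.

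**4. How often would a trial be that close?** I summed the two binomial probabilities over all pairs of failure counts that fail with everyone included and pass once one nalbuphine failure is removed, with morphine at 90%.

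| Per arm | True nalbuphine rate | Passes with no exclusion (Wald; Newcombe) | Fails, but flips on one exclusion (Wald; Newcombe) |
|---|---|---|---|
| 142 | 90% | 80.6%; 77.8% | 4.7%; 5.6% |
| 142 | 80% | 2.8%; 2.5% | 1.1%; 1.0% |
| 158 | 90% | 84.0%; 82.9% | 4.5%; 3.7% |
| 158 | 80% | 2.6%; 2.6% | 1.2%; 1.0% |

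The last column is the share of trials in which one such exclusion would matter. It is not the share in which it would happen.

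**5. Which set is affected?** A nalbuphine failure has been dosed and has an NRS value, so {19} and {20a} keep that patient in the FAS. Calling a violation major removes the patient from the PPS only. The FAS result in step 2 stays at -10.2% and still fails.

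**The case against.** **The FAS does not move.** This stands, and it limits the point. A reader might infer that one exclusion can turn the trial's overall result from failure to success. The documents do not support that: the FAS rule leaves almost no room for judgement, and the flip is shown only for the PPS. The article does not say which set governs if the two disagree. The statement in {20c} that non-compliance and missing data will not be used sits badly with the FAS rule, but that is a separate conflict and nothing here relies on it.

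**Any cut-off has results one patient away from it.** This also stands. The example is a boundary case, and its frequency has to be read with it.

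**Blind review and the definition of a major violation are normally left to the analysis plan.** That is right, and their absence from the article is not held against it. The point rests on what {17a} affirmatively states.

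**Masking does not cure everything.** A reader might infer that it would also settle the open choice of test, since the secondary scores "are compared by the *t*-test or rank-sum test". It would not: a two-sided P-value is the same with arms coded A and B, so naming the test in advance is what settles that. Nor can a later masked review undo a withdrawal under {11b} by an investigator who knew the arm.

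**The rating itself.** The NRS score is chosen by the patient, who is blinded. The point concerns data handling, not how pain is scored.

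**Conclusion.** The point holds in a limited form. By its own statement, {17a} leaves the statistician and the reviewers of set membership unmasked, and the per-protocol analysis of the primary endpoint is exposed to decisions made with arm and outcome in view. Near the margin, one excluded nalbuphine failure moves the lower limit from -10.2% to -9.5%. About 5% of trials at the design rates would lie in that zone, and about 1% if nalbuphine is truly at 80%.

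These figures assume 142 per arm in the per-protocol set before the exclusion, a true morphine rate of 90%, independent binomial outcomes, and no offsetting exclusion on morphine. Nothing in the documents suggests that such an exclusion is intended. This is an inexpensive improvement to the plan, not a flaw that defeats it.

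**What to change.** Amend {17a} so that the statistician and those who review analysis-set membership are masked to arm until the FAS, PPS and SS lists are fixed and signed. The sign-off should cover any decision, made after the data are in, that a prohibited drug prevented evaluation. Release the allocation code to the statistician only after that.

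The cost is one paragraph, a dated review step before database lock, and access control in the electronic system. The last needs checking: {16b} refers to a web response system, whereas {16c} has the data capture system generate the sequence, so it must be confirmed that the code can be withheld from people who work with the data. Ward staff need not be masked for this change, but it will not remove bias from withdrawals they make during the trial.

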### Procedure for unblinding if needed {17b}

When a serious adverse event occurs, the investigator decides whether to unblind.

## Data collection and management

### Plans for assessment and collection of outcomes {18a}

#### Main study outcomes

The NRS was used for assessment, and the NRS consisted of 11 numbers with the same interval from 0 to 10, with 0 representing “no pain” and 10 representing “most intense pain.” Patients chose one number to represent the pain intensity at their score. NRS score (at rest) ≤ 3 points at all assessment time points was considered as effective analgesia and was assessed at 1 min, 5 min, at the end of surgery, and at 2 h, 6 h, 12 h, 24 h, and 48 h after the start of ablation.

#### Secondary outcomes

Pain intensity: Pain intensity was assessed by NRS at 1 min and 5 min after the start of ablation, at the end of surgery, and at 2 h, 6 h, 12 h, 24 h, and 48 h after surgery (at rest, during coughing, or during activity). Analgesic satisfaction: Evaluation of the degree of analgesic satisfaction. (A) Before leaving the operating room to assess the patient’s satisfaction with the analgesic effect; (B) before leaving the operating room, the surgeon and surgical nurse implement the satisfaction assessment; the satisfaction score uses the VAS, with a vernier ruler of 10 cm in length, marked with 10 scales, 0 point and 10 points at both ends, respectively, so that the patient, surgeon, and surgical nurse can mark the corresponding position that can represent their comfort on the ruler, and the follower can score it according to the position marked by the patient. A score of 0 represents extreme dissatisfaction and a score of 10 represents extreme satisfaction. Quality of life: One week after surgery, quality of life was assessed by telephone (using EORTC Quality of Life Inventory QLQ-C30 (V3.0).

We also collected patient demographics, history, physical and laboratory examinations, and surgical information, including tumor type, number of tumors ablated, size and location of lesions, and ablation technique.

All of these informations were recorded in the Case Report Form.

### Plans to promote participant retention and complete follow-up {18b}

We will manage the subjects. (1) Patients were screened according to the inclusion and exclusion criteria of the study using an open recruitment approach. (2) The investigator collects personal data such as the subject’s name, contact information, home address, disease history and pain history in a timely manner. (3) The informed consent should follow the Standard Operating Procedures for Signing Informed Consent, and the investigator respects the subject's right to decide whether or not to participate in the trial, either voluntarily or after consultation with family members, after fully informing the subject about the trial. (4) Arrange follow-up visits for subjects during the trial and complete all examinations in strict accordance with the protocol. (5) Educate subjects not to use drugs prohibited in the trial on their own and to inform the investigator of information related to the combined use of drugs (e.g., name of drug, dose, duration of use, reason for use) in a timely manner at the time of follow-up. (6) Educate the subject that other tests and treatments are required due to the combination of other diseases, and inform the investigator promptly or at the next follow-up visit, and the investigator should record the relevant information promptly after learning it. (7) Inform subjects of possible adverse reactions during the study, and if any physical discomfort occurs during the course of the trial, inform the investigator in a timely manner so that the investigator can decide on a treatment plan. (8) Inform the subjects that their information during the study period will be kept confidential by the investigator and that the subjects are required not to freely divulge the trial study information to the public.

### Data management {19}

An electronic data capture system is used for data collection in this study. According to the GCP requirements for clinical trials in China, the data shall be maintained for 5 years after the termination of the clinical trial.The full analysis set (FAS) of the analysis dataset includes all subjects who were randomized, received the study drug, and had at least one efficacy evaluation data after medication. In case of missing data of the primary efficacy endpoint, the last observation carried forward is applied according to the intention-to-treat principle. The missing values for the comparability analysis and secondary efficacy measures are not carried forward and were based on the analysis dataset obtained in the FAS.Per protocol set (PPS) is a dataset generated from subjects who are fully compliant with the trial protocol; compliance includes receiving treatment, availability of the primary endpoint measures, and no major trial protocol violations. The per-protocol analysis is used mainly for the primary efficacy measures.Safety set (SS) refers to all subjects who are randomized, received the study drug, and have at least one post-baseline safety assessment.

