### Outcomes {12}

#### Main study outcome

Analgesic effective rate: Analgesic effective rate = number of patients with effective analgesia/total number of cases × 100%. NRS score (at rest) ≤ 3 points at all assessment time points is considered as effective analgesia and assessed at 1 min and 5 min after ablation, at the end of the surgery, and at 2 h, 6 h, 12 h, 24 h, and 48 h after surgery. The NRS is used for assessment, which consists of 11 numbers with the same interval from 0 to 10, with 0 representing “no pain” and 10 representing “most intense pain.” Patients are asked to choose one number to represent the pain intensity score.

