## Statistical methods

### Statistical methods for primary and secondary outcomes {20a}

All subjects who were randomized, received the trial drug, and had data on at least one post-dose efficacy evaluation were included in the outcome analysis. The number of different organ tumors, single or multiple tumor tissues, and different ablation techniques were compared between the two groups to determine whether they were comparable.

Statistical analyses are performed using the SAS 9.4 software. Unless otherwise specified, the level of statistical significance was set at *P* ≤ 0.05. For a non-inferiority test, a one-sided test will be used, and *P* ≤ 0.025 are considered statistically significant.

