### Methods in analysis to handle protocol non-adherence and any statistical methods to handle missing data {20c}

Not applicable. Non-compliance with the protocol and missing data, we plan not to use as part of the statistical analysis.

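### The protocol states two incompatible rules for missing primary-endpoint readings, and carrying forward does not suit an endpoint that requires NRS ≤ 3 at every time point

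*Protocol article*

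**What the plan says.** The primary endpoint (Main study outcome) is a responder rate: "NRS score (at rest) ≤ 3 points at all assessment time points is considered as effective analgesia". There are eight scheduled readings: 1 min and 5 min after ablation, end of surgery, and 2, 6, 12, 24 and 48 h. The rate is the "number of patients with effective analgesia/total number of cases".

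On missing readings the protocol says two things:

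- Data management {19}, under the full analysis set (FAS): "In case of missing data of the primary efficacy endpoint, the last observation carried forward is applied according to the intention-to-treat principle".
- Section {20c}, the item meant for non-adherence and missing data, is marked as not applicable and continues: "Non-compliance with the protocol and missing data, we plan not to use as part of the statistical analysis".

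Three other places bear on the choice:

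- Section {20a} says that randomised, treated patients who "had data on at least one post-dose efficacy evaluation were included in the outcome analysis". Patients with incomplete readings are therefore kept.
- The per protocol set (PPS) is restricted by compliance, and "compliance includes receiving treatment, availability of the primary endpoint measures, and no major trial protocol violations". Patients with incomplete readings are therefore removed.
- Section {11b} disenrols patients for "inability to complete the observation due to adverse events" and for "combination of prohibited drugs during the study period that prevented satisfaction and effectiveness evaluation".

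**The concern.** The conflict concerns the primary analysis, so two analysts following the same protocol could report different effective rates. Section {17a} blinds only the patients, so an open choice of rule rests with staff who may know the allocation.

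The rule that is stated, last observation carried forward (LOCF), has its own problem. A patient with low readings up to the end of surgery who then leaves the trial is scored as effective at 2 to 48 h, although nobody measured it. One reading of 4 or more already settles a failure, so LOCF cannot create a wrong failure. It can only err towards success.

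The disenrolment reasons include adverse events and prohibited drugs, and section {11d} bars newly added analgesics. Loss can therefore be related to pain. Non-inferiority is declared when the lower 95% limit exceeds −10%, so a rule that shrinks a true deficit raises the chance of a false claim.

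**Working it through.** **Plan's own figure.** Inputs from Sample size {14}: 90% v 90%, margin 10 points, one-sided α 0.025, power 0.80, ratio 1:1.

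n per arm = (1.960 + 0.842)² × (0.9×0.1 + 0.9×0.1) / 0.10² = 141.3, so 142 per arm and 284 in total. 284 / 0.9 = 315.6, so 316, or 158 per arm. The stated figures reproduce.

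**The two rules side by side.** Section {20c} is garbled. It may mean that patients with incomplete readings are excluded, or that no missing-data method is used. Either reading conflicts with LOCF in {19}. Exclusion also conflicts with {20a}, which keeps anyone with one post-dose evaluation, and with the all-cases denominator of the endpoint.

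**Effect of LOCF.** Take a true 80% (nalbuphine) v 90% (morphine), a deficit exactly at the margin. Let qN and qM be the shares of eventual failures lost before their first NRS of 4 or more. These shares are assumptions; the protocol gives none. Each such patient is scored a success, so:

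- nalbuphine rate = 0.80 + 0.20 qN
- morphine rate = 0.90 + 0.10 qM
- difference = −0.10 + 0.20 qN − 0.10 qM

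With equal shares q this is −0.10 × (1 − q), so the deficit always shrinks. It is unchanged when qM = 2 qN and widens when qM exceeds that.

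Exact binomial enumeration, 158 per arm, Wald 95% lower limit above −10%:

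| qN | qM | Difference (points) | False non-inferiority |
|---|---|---|---|
| 0 | 0 | −10.0 | 2.6% |
| 10% | 10% | −9.0 | 4.8% |
| 25% | 25% | −7.5 | 11% |
| 50% | 50% | −5.0 | 41% |
| 50% | 0 | 0.0 | 84% |
| 10% | 20% | −10.0 | 2.8% |
| 10% | 30% | −11.0 | 1.5% |
| 0 | 50% | −15.0 | about 0.05% |

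Ten percent loss unrelated to outcome in both arms gives the same expected LOCF rates as q = 10%, because lost successes stay successes. The error is again about 4.8%.

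**Effect of dropping patients.** If only failures are lost, the rate is p / (p + (1 − p)(1 − q)). At q = 50%: 0.80/0.90 − 0.90/0.95 = 88.9% − 94.7% = −5.9 points (unrounded −5.85), and the simulated error is 27%. At q = 25% it is −8.1 points and 8%. With 10% loss unrelated to outcome, the difference stays at −10.0 points and the error is 2.8%; at a true 90% v 90%, power falls from 84% to 80%.

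**Loss concentrated in morphine.** At a true 90% v 90%, if half of morphine's failures alone are lost, power falls from 84% to 41% under LOCF and to 43% under dropping.

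**The case against.** A reader might infer that both rules always favour non-inferiority. The documents do not support that. The Background cites adverse effects that lead many patients to give up morphine, and fewer side effects with nalbuphine; {11b} withdraws patients for adverse events. Morphine could therefore lose the larger share of its failures, and the last three rows of the table show the bias cancelling or reversing. Dropping is unbiased when loss is unrelated to outcome. This part of the objection stands.

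A reader might also take the planned 10% dropout as support for the assumed shares. It is not: the plan's 10% is of all patients, not of failures, and it may include patients who never enter the FAS. The 50% row corresponds to overall loss of 10% and 5% in which every lost patient is a failure.

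Three of the eight readings fall at or before the end of surgery, and the pain scores cited in the Background are intraoperative. Many failures may be recorded before anyone leaves. If only 3% to 5% of failures are lost first (assumption), the error is 3.2% to 3.6%.

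Loss through discharge before 48 h is tempting to add, but no section says that patients leave that early.

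Finally, the PPS gives an analysis without LOCF beside the FAS. It is not a safeguard, because it requires the primary endpoint measures and so removes patients with incomplete readings.

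**Conclusion.** The contradiction between {19} and {20c} is plain in the text and needs no assumption. An unseen analysis plan would not cure it, since the protocol itself states both rules.

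That LOCF can err only towards success on this endpoint follows from the definition. How far this moves the result is conditional. When failure-related loss is similar across arms or greater with nalbuphine, a true deficit at the margin shrinks, and with equal shares the error runs from 4.8% to 41% over the assumed range of 10% to 50%, against 2.6% with no loss. When morphine loses more than twice nalbuphine's share at these rates, LOCF works against nalbuphine. The stated rule can therefore give a wrong primary result in either direction. It should be changed before analysis.

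**What to change.** Delete the sentence in {20c} and replace LOCF in {19} with one primary rule, stated once:

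1. Any observed resting NRS of 4 or more makes the patient a failure, whatever is missing afterwards.
2. Other missing readings are multiply imputed within arm from the patient's own NRS readings, and the all-time-points endpoint is derived from the imputed data.

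Add sensitivity analyses with arm-specific assumptions: a tipping point that worsens only the nalbuphine arm, and one that scores stops for lack of effect or added analgesics as failures.

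Do not score all adverse-event withdrawals as failures in the primary analysis. At a true 80% v 90%, suppose 2% of nalbuphine and 5% of morphine patients withdraw for adverse events unrelated to pain (assumption). The rates become 0.80 × 0.98 = 78.4% and 0.90 × 0.95 = 85.5%, and false non-inferiority is 10%. At 5% v 10% they become 76.0% and 81.0%, and it is 19%.

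The cost is protocol wording, a little programming, and slightly lower, less precise effective rates.
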